## Abstract

**Background:**

Negative symptoms of schizophrenia are frequently associated with poor long term outcomes. Established interventions have little, if any, positive effects on negative symptoms. Arts Therapies such as Body Psychotherapy (BPT) have been suggested to reduce negative symptoms, but the existing evidence is limited. In a small exploratory trial a manualised form of group BPT led to significantly lower negative symptom levels both at the end of treatment and at 4 months follow-up as compared to supportive counseling. We designed a large multi-site trial to assess the effectiveness of a manualised BPT intervention in reducing negative symptoms, compared to an active control.

**Methods/Design:**

In a randomised controlled trial, 256 schizophrenic outpatients with negative symptoms will be randomly allocated either to BPT or Pilates groups. In both conditions, patients will be offered two 90 minutes sessions per week in groups of about 8 patients over a period of 10 weeks. Outcomes are assessed at the end of treatment and at six months follow-up. The primary outcome is severity of negative symptoms, as measured by the Positive and Negative Symptom Scale (PANSS), whilst a range of secondary outcome measures include general psychopathology, social contacts, and quality of life. We will also assess the cost-effectiveness of the intervention.

**Discussion:**

The study aims to evaluate the effectiveness of a promising form of group therapy which may help alleviate negative symptoms that are associated with unfavourable long-term outcomes and have so far been difficult to treat. If the trial is successful, it will add a new and effective option in the treatment of negative symptoms. Group BPT is manualised, might be attractive to many patients because of its unusual approach, and could potentially be rolled out to services at relatively little additional cost.

**Trial registration:**

Current Controlled Trials ISRCTN84216587

## Background

Despite improvements of anti-psychotic medication and psychological treatments, schizophrenia patients often experience persistent symptoms and full remissions are infrequent. Patients often do not adhere to existing pharmacological and psychological treatments and even when they do, currently available treatments have an only limited effect. This applies in particular to negative symptoms which are frequently associated with poor long term outcomes.

The National Institute for Clinical Excellence (NICE) reviewed the literature on the treatment of negative symptoms and identified six trials using different forms of ‘arts therapies’. Arts therapies is an umbrella term including therapies that have central non-verbal components, such as Body Psychotherapy (BPT). NICE suggested that arts therapies are effective in reducing negative symptoms as compared to any other control. The Guideline Development Group recommended that “further large-scale investigations of arts therapies should be undertaken to increase the current evidence base” [1] (p199). In particular, “an adequately powered trial should be conducted to investigate the clinical and cost-effectiveness of arts therapies as compared to an active control in people with schizophrenia” [1] (p200).

BPT refers back to a long tradition in psychiatry. A first trial in schizophrenia patients was published in 1965 showing a significant improvement of the treatment group, as compared to controls in affective contact, motility and general functioning [2]. Four further controlled studies - three of them randomised - compared forms of BPT with non-specific attention, music therapy or fitness training. The results suggest favourable effects of the experimental treatments on a range of outcome variables, including some indicators of negative symptoms [2-5]. However, all these studies, which were exclusively conducted before 1980, have serious methodological shortcomings such as small sample sizes, vaguely defined outcome criteria, no systematic assessment of psychopathology, no recording of medication, and no intention-to-treat analysis.

A more recent exploratory randomised controlled trial tested manualised BPT in out-patients with persistent negative symptoms of schizophrenia [6]. Compared to a control group receiving supportive counselling, patients in the experimental group showed a significant improvement of negative symptoms. The effect size was large, and maintained at a 4 month follow up. The major limitations of that study were that it was a small exploratory trial based at one site and with only one BPT therapist, and that the control condition was supportive counselling, which turned out to be unattractive to patients and meant that the non-specific effects of physical activity could not be controlled for. In addition, the exploratory study did not provide sufficient evidence for the cost-effectiveness of BPT. Following these findings, an open uncontrolled trial of manualised BPT was conducted by the same authors with different therapists which yielded similar results [7], however to date there have been no other rigorous trials on BPT or a similar method in the treatment of schizophrenia [8].

The specific components of the BPT under investigation are a) the focus on body experience at a cognitive and emotional level b) the facilitation of emotional group interactions, and c) the link between movement and emotion. The manual for BPT [9], which was applied in the exploratory trial and will also be used in this pragmatic trial, intends to utilise the three specific mechanisms. Common components utilised in both interventions will include the non-specific effects of non-emotional group interactions, therapist/instructor attention, and physical activity.

In a review into physical exercise for schizophrenia [10], physical activity groups were found to significantly improve depression scores and negative symptoms in comparison to treatment as usual, but in a study which used physical activities as an active control designed to evaluate the effectiveness of yoga therapy [11] yoga was found to result in a significantly greater reduction in negative symptoms in comparison to physical activity alone. This study suggests that physical activity groups can be used as an active control, fulfilling the requirement laid down by NICE for a ‘sham condition’, but with physical activity groups being found to have a significant effect on negative symptoms this study may under-report any effect of the intervention compared to the usual treatment patients are likely to receive.

Beyond the expected clinical effectiveness, there are three characteristics of BPT that make it particularly beneficial for service providers: 1) as a group based method, BPT is relatively inexpensive; 2) BPT can be flexibly combined with other treatment methods including all pharmacological interventions; 3) because BPT is so distinct from conventional treatment methods, it can appeal to patients who are difficult to engage in other forms of treatment. The latter point is underlined by findings of a qualitative evaluation of the exploratory trial [7] in which patients fed back most positively about both its focus and methods.

## Methods

### Study Design

In a randomised controlled trial, schizophrenia patients with negative symptoms will be randomly allocated to groups for BPT or Pilates as an active control. Both conditions are in addition to treatment as usual and will be delivered in groups of about 8 patients each. There will be 3 data collection points; before treatment, after the 10 week treatment period, and after a 6 month follow-up period. Each therapist in either condition will run a maximum of two groups, and in each group they will be assisted by a co-facilitator. The trial cannot be fully “blind” because clinicians and patients cannot be masked towards the allocation of the patients to the experimental or control group. However, researchers who conduct the outcome assessments will be masked to the allocation of patients, and the eligibility and baseline assessments will occur pre-randomisation. All the analysis will be conducted blind to the participant allocation.

Originally, the plan was to randomise 16 patients at a time in each site, eight to intervention and eight to control, but this was changed for logistic reasons. We will now recruit a larger number, i.e. up to 20 patients in one batch, to ensure we have a sufficient number of participants randomised to cover any dropout between the eligibility and baseline assessment phases. After the baseline assessments, participants will be randomly allocated to the intervention or control group in batches using randomly permuted blocks of 4 and 6, starting each batch at the start of a new block to preserve balance. Conducting the randomisation in this manner allows us to randomise all the participants in one batch either at the same time or over two time points, allowing the research team more time to finalise the logistics involved with getting all the participants to the groups at the correct times.

BPT and Pilates groups will both run for 10 weeks. After the 10 week intervention period and after a further 6 month follow-up patients will be interviewed by the researchers and outcomes will be assessed. These assessments will be conducted either on NHS sites or in the community, ideally in the same location as the original assessments.

### Planned interventions

Patients in the experimental group will receive 20 sessions of BPT which will be delivered in groups of approximately 8 patients over a 10 week period. Each session will take 90 minutes.

BPT is manualised with the following components: 1) overcoming communication barriers through non-verbal techniques; 2) re-focussing cognitive and emotional awareness towards the body; 3) stimulating activity and emotional responsiveness; 4) exploring physical potentials; 5) focussing on strength and experiencing the body as a source of creativity, reliability, pleasure and self-expression; 6) modifying dysfunctional self-perception and addressing body-related psychopathological features such as boundary loss, somatic depersonalisation, and body schema disturbances.

Each BPT session contains five discrete sections; 1) the opening circle, which is used to describe feelings and energy levels; 2) a warm-up section, where participants stand in a circle and warm up using different body parts and movements; 3) a structured task section, which includes exercises such as mirroring each other’s movements and creating body image sculpture in partners; 4) a creative movements section, which includes exercises such as creating group sculptures and reflecting on perceptions and emotions; 5) a closing circle, used to reflect on the group experience and to refocus on the self with body oriented exercises. More detail on this is available in the manual [9].

All therapists will be accredited dance-movement psychotherapists with additional training in applying the manual of body psychotherapy for patients with negative symptoms of schizophrenia, as it was used in the exploratory trial [6]. Regular supervision will be provided 3 times within each 10 week treatment period. Adherence to the manual will be assessed by the author of the manual based on videotapes of the sessions.

The active control condition of Pilates groups will be delivered with the same frequency and length of sessions and overall duration as BPT, i.e. there will be two sessions per week over a ten week period and each session will last up to 90 minutes. Pilates groups will be described to patients as a fitness and physical health intervention so that in the recruitment process patients consent to participate in one of two interventions that share several elements, most importantly the format and physical activities. This is intended to limit the risk of different acceptance rates of the two interventions once patients are informed about their allocation.

The venues for the Pilates groups will be similar rooms as those used for BPT. Pilates groups will be delivered by qualified instructors supported by a co-facilitator, and follow the established guidelines for such groups. A brief manual for the Pilates groups was written by qualified instructors involved in the trial, in collaboration research team, using the Pilates Union Matwork Manual as a guide [12]. The Trial manual contains instructions on how to run the groups, as well as references to material describing the exercises in detail. Group interactions will occur as they commonly do when patients are together, but the instructor will not actively encourage or structure them. Instructors will pay attention to patients and respond to them without addressing or verbalising emotions. As an active control condition in this trial, Pilates will therefore provide moderate physical activity, instructor attention and non-emotional group interaction, but not the specific components of BPT which are the focus on body experience, the facilitation of emotional group interactions, and linking movement and emotional experience. In both conditions the same therapist or instructor will be in charge of a maximum of two groups.

### Inclusion criteria

The inclusion criteria for community patients receiving mental health care in services in the National Health Service (NHS) are as follows: 

Being aged between 18 and 65 years.

Having an established diagnoses of schizophrenia according to DSM-IV.

Having had symptoms of schizophrenia for at least 6 months.

Having Scores of ≥18 on the negative symptoms subscale of the Positive and Negative Symptom Scale; the PANSS [13].

Not changing the type of anti-psychotic medication prescribed for at least 6 weeks prior to recruitment (although dosage may change).

A willingness to participate in groups for BPT or physical activity.

An ability to give written informed consent.

### Exclusion criteria

The exclusion criteria are: 

Severe physical disability preventing patients from participating in groups for BPT or Pilates.

Insufficient command of English so that outcomes cannot be reasonably assessed in English.

A physical condition that makes participation in either BPT or Pilates impossible or potentially. harmful.

### Outcome measures

The primary outcome criterion for the effectiveness of BPT is the level of negative symptoms as assessed on the PANSS [13].

The secondary outcomes are: 

The levels of general psychopathology and positive symptoms, measured by the PANSS [13].

Subjective quality of life, measured by the Manchester Short Assessment of Quality of Life [14].

A measure of the amount activities the participant has engaged in during the previous week, using items from the Time Use Survey [15].

The participants level of treatment satisfaction in the intervention, measured by the Client Satisfaction Questionnaire [16].

A measure of the participants objective social situation, recorded by the SIX [17].

Extrapyramidal symptoms, using the Simpson-Angus Scale [18].

A secondary measure of negative symptoms which has been developed recently and attempts to differentiate between measures of emotional experience and emotional expression (Clinical Assessment interview for Negative Symptoms; the CAINS, [19]).

A measure of nonverbal communication/gesture behaviour, based on videotapes of the assessments using the NEUROGES-ELAN system [20].

A measure of Depression (the Calgary Depression Scale [21]).

The level of social contacts the participant has made in the past month, measured through using sections of the Social Network Scale [22].

A measure of cost-effectiveness using the Client Service Receipt Inventory (CSRI, [23]).

A measure of Quality of life adjusted years, based on the EQ-5D [24].

All criteria will be obtained at pre-treatment baseline, at the end of treatment, and after a 6 month follow-up. Our primary hypothesis relates to endpoints at the end of treatment.

The number of therapy sessions attended by patients in both groups will be recorded. Costs of BPT and Pilates will be calculated taking into account the staff time involved in delivering therapy, training received and supervision (including time of both therapists and those providing training/supervision). The training costs will be apportioned over the period of time in the trial during which therapy is delivered. However, the benefits of training are likely to run beyond the trial and therefore sensitivity analyses will involve apportioning training costs over longer periods. Other service use information (including health and social care inputs, medication and informal care) will be collected for the 6 months prior to treatment, the treatment period of 10 weeks, and the 6 month follow-up period using the CSRI [23]. Service use data will be combined with nationally applicable unit costs. Informal care costs will be based on the unit cost of a homecare worker, with wage rates for employed carers used as an alternative in sensitivity analyses. Costs will be reported in line with NICE guidance.

### Ethics Approval

The study has been approved by the Camden & Islington National Research Ethics Committee (REC reference 10/H0722/44)**.** All data will be stored in line with the Data Protection Act. All video-recorded data will be encrypted and password protected.

### Trial Steering Committee and Data Monitoring and Ethics Committee

Both a Trial Steering Committee (TSC) and Data Monitoring and Ethics Committee (DMEC) have been established.

### Recruiting participants and obtaining informed consent

In order to recruit participants clinicians will be asked to screen their caseloads to identify those eligible and appropriate for the study, and then to ask them for their consent to be approached by a research assistant. If the patient agrees, they will be contacted by a member of the research team, fully informed about the study, and asked for written informed consent. Once the participant has consented, the researcher will then conduct the eligibility assessment. Consent to take part in the trial can be withdrawn at any time, without any negative consequences, other than that patients would not have the potential benefits of further participation in the BPT or Pilates groups. As part of this process we will request consent for the pre and post intervention PANSS & CAINS interviews to be video recorded to enable independent researcher ratings as well as further analysis of the data. This is optional for patients, and if they do not wish to be video-recorded this will not impact on their participation in the study.

### Statistical analysis

The primary analysis will be an available case analysis following intention to treat principles. We will use mixed effect models as appropriate to the outcome, with fixed effects for the intervention, baseline level of outcome and centre, and random effects for therapy groups. For continuous outcomes we will use Stata’s *xtmixed* command, *xtmepoisson* for count outcomes, and *gllamm* for ordinal outcomes. We will assess whether there is a clustering effect due to therapist or instructor (some therapists or instructors will lead two groups), but will not take this element of clustering into account in the analysis.

We will use sensitivity analyses to explore the impact of any missing data, including extreme scenario sensitivity analyses, for example that those who are lost to follow up would have no improvement as result of any intervention. If there are sufficient missing values to warrant its use, we will use multiple imputation following an exploration of patterns of missingness. We expect to use the MAR (missing at random) assumption in this imputation. In case group dropout (as opposed to study dropout) is higher in one condition compared to the other, we will conduct a simple complier-average causal analysis with compliers defined by the active intervention. Compliance will be defined as attendance of five or more sessions of BPT.

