### Proposed sample size

A 20% reduction in the PANSS negative scale has been defined as clinically significant [25], which we would anticipate to be a difference of approximately 3 points given the eligibility criteria. To detect a difference of 3 points, with a standard deviation of 5, at alpha = 5%, and a power of 90%, 58 patients are required in each arm. Assuming an intra-cluster correlation coefficient for treatment group of 0.1, and 7 patients per group with analysable data at the end of treatment gives an inflation factor of 1.6 [24] leading to a required sample size of 93 in each arm. At six months we expect a loss to follow-up of 31%, resulting in 5.5 individuals per group on average and an inflation factor of 1.45; recruiting 128 per arm (16 groups of 8 in each arm) leaves 88 per arm at 6 months and 91% power to detect a difference of 3 points at this time point (see Figure 1). One hundred and twenty eight patients per arm, i.e. 16 groups of approximately 8 patients in each arm will give 94% power for the end of treatment analysis. We do not expect to recruit and allocate exactly eight individuals within each group but the variation in group size will be small and will not materially affect the power of the trial.

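### As the model is listed, the secondary 6-month PANSS comparison leaves out the end-of-treatment scores of patients lost later, which costs a little precision and can bias it if loss differs by arm

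*Protocol article*

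**What the plan says.** Under Statistical analysis the protocol article says: "The primary analysis will be an available case analysis following intention to treat principles". The mixed models are specified "with fixed effects for the intervention, baseline level of outcome and centre, and random effects for therapy groups". Neither a visit term nor a patient-level effect is listed.

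The same section promises sensitivity analyses for missing data, including extreme scenarios such as no improvement in those lost. It adds multiple imputation under a missing-at-random assumption if there are enough missing values to justify it. No threshold is given, and the variables in the imputation model are not named.

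On timing, Outcome measures says: "All criteria will be obtained at pre-treatment baseline, at the end of treatment, and after a 6 month follow-up". It then adds: "Our primary hypothesis relates to endpoints at the end of treatment". The 6-month comparison is therefore secondary, although Proposed sample size gives it its own power figure. That section assumes "7 patients per group with analysable data at the end of treatment" (of 8 allocated) and, later, "At six months we expect a loss to follow-up of 31" per cent, leaving 88 per arm.

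**The concern.** Two post-treatment PANSS scores per patient cannot properly share a model that has no visit term and no within-patient correlation. The natural reading is one model per visit. The 6-month model then adjusts for baseline but not for how the patient stood at the end of treatment, and a patient last seen at the end of treatment contributes nothing to it.

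Two things are at stake at 6 months. The first is precision, because the end-of-treatment score carries information about the missing 6-month score. The second is bias. The single-visit model is valid if loss depends only on baseline, centre, therapy group and arm. If loss also depends on the observed end-of-treatment score, the data can still be missing at random, which is the assumption the plan expects to use for imputation. The single-visit model nevertheless omits the variable that drives the loss.

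**Working it through.** **Inputs from the protocol (Proposed sample size):** difference 3, SD 5, alpha 5% (taken as two-sided), ICC 0.1, 16 groups of 8 per arm, 7 analysable per group at end of treatment, 5.5 at 6 months.

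**Assumptions not in the protocol:** correlation ρ between the two post-treatment scores given baseline, 0.4–0.7; monotone loss; odds of later loss changing by a factor of 2 per 5 PANSS points at end of treatment; baseline correlation 0.5.

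**1. The plan's own figures.**
- Unadjusted n per arm: (1.960 + 1.282)² × 2 × 25 / 9 = 58.4 (stated 58).
- Inflation factors: 1 + 6 × 0.1 = 1.6 and 1 + 4.5 × 0.1 = 1.45. Then 58 × 1.6 = 92.8 (stated 93).
- End of treatment: n = 16 × 7 = 112, SE = 5 × √(2 × 1.6 / 112) = 0.845, power Φ(3/0.845 − 1.96) = 94.4% (stated 94%).
- 6 months: n = 128 × 0.69 = 88.3, SE = 5 × √(2 × 1.45 / 88) = 0.908, power 91.1% (stated 91%).

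All reproduce. The 91% already rests on the 88 available cases.

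**2. Scores not used.** 112 − 88 = 24 per arm, and 24/112 = 21% of those measured at end of treatment.

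**3. Precision.** Without clustering, a joint model multiplies the 6-month variance by 1 − ρ²(1 − 88/112). That is a gain of 3.6% at ρ = 0.4 and 11.7% at ρ = 0.7. Recovering patients within groups does not reduce the between-group part, so this is too high here. At 6 months the variance of a group mean is proportional to 0.1 + 0.9/5.5 = 0.264, of which 0.164 (62%) can be reduced:
- ρ = 0.4: 1 / (1 − 0.62 × 0.16 × 0.214) = 1.022
- ρ = 0.7: 1 / (1 − 0.62 × 0.49 × 0.214) = 1.070

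A full generalised least squares calculation (16 groups per arm, 7 patients at end of treatment, 5 or 6 at 6 months) gives 2.2% and 7.1%. The assumed correlation of group effects over time makes almost no difference. The SE falls from 0.909 to 0.899 or 0.878, and power rises from about 91% to 91.6% or 92.7%. In equivalent sample size, 88 per arm becomes 88 × 1.022 = 90 to 88 × 1.071 = 94.

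**4. Bias.** Simulation with total SD 5, average later loss 24/112, logistic loss on the end-of-treatment score, and a baseline-adjusted 6-month difference. A positive sign means the benefit of BPT is overstated.

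| Dependence of loss on score | ρ = 0.4 | ρ = 0.7 |
|---|---|---|
| Same in both arms, no true effect | about 0 | about 0 |
| Same in both arms, true effect 3 | −0.06 | −0.10 |
| BPT arm only, high scorers lost, true effect 3 | +0.18 | +0.33 |
| BPT arm only, low scorers lost, true effect 3 | −0.25 | −0.43 |
| Opposite in the two arms | ±0.42 | ±0.73 |

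If baseline explains nothing, so that the whole SD of 5 is residual, the figures over the same ρ range are larger: up to 0.14 for the same dependence, 0.24–0.57 for one arm and 0.55–0.97 for opposite dependence. A joint estimate stayed within about 0.01 of the truth throughout. That is expected, since loss was made to depend only on a score which that model includes.

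**The case against.** The strongest reply has four parts.

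*The primary result is not involved.* This stands. A reader might infer from the opening words of the analysis section that the main comparison is compromised. The primary hypothesis is at end of treatment, and this argument concerns only information lost after that visit. The protocol also does not present maintenance at 6 months as a main claim; it only gives it a power figure.

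*No stated figure is wrong.* This also stands. A reader might infer that the 6-month power is overstated, but it was computed on the 88 available cases and reproduces.

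*The plan already deals with missing data.* This stands in part. Sensitivity analyses are promised without condition, and with 31% expected loss imputation may well be triggered. Imputation that includes the end-of-treatment score would recover the same information. But it remains conditional, and its variables are not stated. The example scenario of no improvement in those lost would override improvement actually observed at end of treatment in patients who leave later.

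*The article is condensed.* It never says that the visits are modelled separately, and an analysis plan may settle the matter. That makes the reading an inference, but one drawn from an explicit list of terms. Letting the model vary with the outcome, as the section does, concerns continuous, count and ordinal data and not repeated visits. A baseline-adjusted model per visit is a standard choice, so this is a matter of a better method rather than an invalid one.

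**Conclusion.** The point holds as a modest weakness of the secondary 6-month PANSS comparison. As listed, the model does not use the end-of-treatment scores of about 24 patients per arm. The cost in precision is about 2–7% in equivalent sample size for ρ of 0.4–0.7 with ICC 0.1.

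It would be too strong to say that the 6-month effect is biased whenever loss depends on the end-of-treatment score. With the same dependence in both arms, bias is nil under no effect and at most about 0.15 points toward the null under a 3-point effect. Material bias needs dependence that differs by arm: roughly 0.2–0.4 points for one arm and 0.4–0.7 for opposite directions. It can inflate or shrink the effect, and compares with a 3-point target and an SE of about 0.91. The protocol says that low motivation is part of severe negative symptoms and allows for unequal group dropout, so the risk is reasonable to guard against. Nothing in it shows that such a pattern will occur.

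The correlations, the odds ratio of 2, the baseline correlation and monotone loss are all assumptions. A larger residual SD or a higher ρ would raise the bias figures.

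**What to change.** Estimate the 6-month contrast from one linear mixed model of both post-treatment PANSS scores, with arm by visit, baseline by visit, centre, random therapy-group effects and within-patient correlation. Keep the end-of-treatment contrast as primary, and the single-visit available-case model as a sensitivity analysis. Alternatively, commit now, without a trigger, to multiple imputation that includes the end-of-treatment score by arm.

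The cost is a few lines of analysis-plan wording and a slightly more complex model with a covariance assumption. No new data are needed and the sample size does not change. Neither option protects against loss that depends on the unobserved 6-month score, so the extreme-scenario analyses should stay.

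### Randomisation is blocked within batch but the primary model omits batch, so any variance shared by a batch's two groups inflates the reported standard error; the size depends on a batch variance the protocol does not give

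*Protocol article*

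**What the plan says.** **Randomisation (Protocol article, Study Design).** Participants are allocated "in batches using randomly permuted blocks of 4 and 6, starting each batch at the start of a new block to preserve balance". The superseded scheme is described in the same section: "the plan was to randomise 16 patients at a time in each site, eight to intervention and eight to control". The current scheme recruits "up to 20 patients in one batch" to cover dropout before baseline assessment, and groups still have about 8 patients.

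**Analysis (Protocol article, Statistical analysis).** Mixed models are to be fitted "with fixed effects for the intervention, baseline level of outcome and centre, and random effects for therapy groups". The section adds that clustering by therapist or instructor will be examined but not modelled. It does not mention batch.

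**Sample size (Protocol article, Proposed sample size).** The calculation uses a 3-point difference, SD 5, an ICC of 0.1 for treatment group and 7 analysable patients per group. It plans 16 groups per arm and states 94% power at end of treatment. The ICC is not divided into a part shared by a batch and a part specific to a group.

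**The concern.** The design balances the arms within batch, but the model gives no credit for that balance. The two groups of a batch are recruited in the same round and, under the superseded scheme explicitly, at the same site. They can therefore share local caseload and season. Centre captures such differences only if they are constant across a centre's batches, and baseline adjustment only as far as they already show in the baseline score.

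What remains raises or lowers both groups of a batch together. It drops out of the BPT minus Pilates difference. A model with only a group-level random effect cannot see the pairing, treats the shared part as independent group noise, and adds it to the standard error. At stake is precision: a real effect smaller than 3 points could be reported as inconclusive.

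**Working it through.** **Inputs from the protocol.** Difference 3, SD 5 (total variance 25), alpha 5% (taken as two-sided), ICC 0.1, 7 analysable per group, 16 groups per arm.

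**Assumptions.** One BPT and one Pilates group per batch, hence 16 batches; 4 centres; a share f of the 0.1 ICC belonging to batch. The protocol gives no value for f, so a range is shown.

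**1. Reproduce the plan's figures.** The unadjusted size is 2 × (5 × (1.960 + 1.282) / 3)² = 58.4 per arm; the plan states "a power of 90%, 58 patients are required in each arm". The inflation factor is 1 + (7 − 1) × 0.1 = 1.6, and 58 × 1.6 = 92.8, or 93. With 16 × 7 = 112 analysable per arm, the effective size is 112 / 1.6 = 70 and power is 94.4%. The stated 94% reproduces.

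**2. Variance components.** Within-group variance is ve = 22.5. Between-group variance is 2.5 = vb + vg, where vb is shared by batch and vg is specific to the group.

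- True variance of the difference: 2 × (vg + ve/7) / 16
- Variance counted when batch is ignored: 2 × (vb + vg + ve/7) / 16

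For f = 0.5, vb = vg = 1.25 and ve/7 = 3.214:

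- True: 2 × 4.464 / 16 = 0.558, SE 0.747
- Counted: 2 × 5.714 / 16 = 0.714, SE 0.845

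Fixed centre effects remove some of vb. With 4 centres, 32 group means leave 32 − 2 − 3 = 27 residual degrees of freedom, and vb enters with weight 2 × (16 − 4) / 27 = 24/27. The counted variance becomes 2 × (1.25 × 24/27 + 4.464) / 16 = 0.697, SE 0.835. This is about 12% above 0.747.

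**3. Type I error at f = 0.5.** By formula, 2 × (1 − Φ(1.96 × 0.845 / 0.747)) = 2.7%. Simulation of group means gave 3.0% with a t reference and 3.8% with a normal reference. A REML simulation with a normal reference gave 3.5%.

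**4. Power at f = 0.5, normal reference, like for like** (1.96 × 0.845 = 1.656).

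- 3 points: planned Φ((3 − 1.656) / 0.747) = 96%; batch modelled Φ(3 / 0.747 − 1.96) = 98%
- 2 points: planned Φ((2 − 1.656) / 0.747) = 68%; batch modelled Φ(2 / 0.747 − 1.96) = 76%

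A simulation with a random batch intercept and normal reference gave 96% against 98% for 3 points and 69% against 76% for 2 points.

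**5. Range over f, t reference, fixed batch effects as the comparator** (200,000 simulated trials per row).

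| f | SE, planned | SE, with batch | Type I error, planned | CI half-width, planned / batch | Power for 3 points, planned / batch |
|---|---|---|---|---|---|
| 0 | 0.845 | 0.845 | 4.9% | 1.72 / 1.77 | 92.8% / 91.3% |
| 0.25 | 0.840 | 0.797 | 3.9% | 1.71 / 1.67 | 94.1% / 94.0% |
| 0.5 | 0.835 | 0.747 | 3.0% | 1.70 / 1.57 | 95.1% / 96.2% |
| 0.75 | 0.829 | 0.693 | 2.2% | 1.68 / 1.45 | 96.3% / 98.1% |

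Fixed batch effects leave 15 degrees of freedom against 27, which explains the loss at f = 0.

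**6. If batch variance comes on top of the 0.1 ICC** (total variance then exceeds the protocol's 25), power for 3 points under the planned model against fixed batch effects is 91.6% / 91.2% at 2% of 25, 89.8% / 91.2% at 5%, and 86.2% / 91.1% at 10%.

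**7. Unequal groups.** A REML run with 5 to 9 patients per group and f = 0.5 reported a mean SE of 0.85 for the planned model and 0.76 with fixed batch effects. The empirical SD of the estimate was 0.83 under both. With only 150 trials its Monte Carlo error is about 0.83 / √300 = 0.05, so this run supports the gap in reported SEs but does not by itself settle the true SE.

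**The case against.** The strongest reply is that nothing here is invalid. Clustering by therapy group is modelled, centre and baseline are adjusted for, and any error is in the conservative direction. That stands.

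It also stands that the key input is assumed. The protocol gives one undivided ICC, and only batch variance left after centre and baseline matters. At f = 0 a fixed batch term loses power, and at f = 0.25 it changes almost nothing. Some candidate sources of shared variance are weak. The protocol does not say that the two groups of a batch share assessors. Waiting time runs from each patient's consent and so varies within a batch. The same research assistant is to interview a patient throughout, so baseline adjustment partly removes stable rater differences.

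Three stronger readings are tempting and not supported:

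- *Batch variance makes the treatment estimate noisier.* With arms balanced within batch it cancels, and with equal groups the estimate is the same with or without a batch term. Only the reported standard error changes.
- *Modelling batch lifts power from the stated 94% to 98%.* The 94% takes no account of shared batch variance. Under the assumption that yields 98%, the planned model already has about 96%.
- *The trial is underpowered because of the omission.* When the batch share is taken from within the 0.1 ICC, the planned model's power rises with that share. It falls only if batch variance is added to the protocol's own variance, for which the protocol gives no basis.

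An SAP could add a batch term. However, the article states the model's terms explicitly, so the omission belongs to a stated specification.

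**Conclusion.** The point holds as a conditional matter of efficiency. Batch restricts the randomisation and is missing from the stated model, and centre cannot represent differences between batches within a centre. Any such variance left after baseline adjustment makes the reported standard error too large.

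If half of the 0.1 ICC is shared by batch, the overstatement is about 12% to 13%, with type I error near 3%. The power cost is then about 2 points at a 3-point effect (about 1 point with fixed batch effects and a t reference) and about 8 points at a 2-point effect. With no batch variance the cost is nil.

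These figures rest on one BPT and one Pilates group per batch (16 groups per arm, the earlier eight-to-eight scheme and groups of about 8 imply it; no sentence states it for the current plan), on 4 centres for the simulated figures, and on an ICC taken before baseline adjustment. A reader might infer that a significant result from the planned model could not be trusted; the conservative direction of the error says otherwise.

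**What to change.** Before unblinding, prespecify a random intercept for randomisation batch in the clinical outcome models, with therapy group nested within batch, and keep baseline and centre as fixed effects. State in the same place that each batch forms one BPT and one Pilates group, if that is so.

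For the continuous primary outcome, also prespecify a small-sample degrees-of-freedom correction such as Kenward-Roger or Satterthwaite, and confirm that the chosen software routine provides it. Without it, simulation of the batch-adjusted model with 16 batches and a normal reference gave type I error of about 5% to 7%, so the change would replace a conservative test with a slightly liberal one.

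The cost is small. Batch is known for every patient and no new data are needed. There is slightly more analysis work and a small loss of degrees of freedom. A random batch term is preferable to fixed batch effects, which would cost about 1.5 points of power (92.8% to 91.3%) if batch variance proved to be zero.
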